### **Data collection**

Outcomes will be assessed using population-level administrative databases linked through unique, encrypted patient identifiers at the Institute for Clinical Evaluative Sciences (ICES). Data will be compiled from the following databases: 1) the Ontario Drug Benefits (ODB) database, covering all prescription medications dispensed to residents in long-term care homes; 2) the Canadian Institute for Health Information (CIHI) databases covering all hospitalizations and emergency department visits; 3) the Ontario Health Insurance Plan (OHIP) database, covering physician billings for procedures and

consultations; 4) the Registered Persons Database covering demographic information including date of death; and 5) the Continuing Care Reporting System (CCRS) database for clinical and demographic information on LTC residents collected using the Resident Assessment Instrument (RAI). Each LTC resident in the province receives a ‘full’ RAI assessment within 2 weeks from admission date, every 12 months from previous full assessment or any other time when the clinical condition of a patient changed considerably and each resident also receives a ‘quarterly’ assessment every 3 months. For each resident, the CCRS database holds demographic and clinical information, including data regarding clinical diagnoses (e.g., dementia, psychosis), dispensing of antipsychotic medications, and occurrences of falls. In addition, a number of validated outcome scales can be derived from the CCRS data, including those related to ADLs, aggressive behaviour, pain, and mood.

The process evaluation involves a mixed-methods approach using individual qualitative interviews and quantitative prescriber surveys.

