### **Outcomes**

The following primary and secondary prescribing and clinical outcomes will be assessed in the trial:

| Variable        | Definition | Source |
|-----------------|------------|--------|
| Primary outcome |            |        |

|                                                   |                                                                                       |                   |
|---------------------------------------------------|---------------------------------------------------------------------------------------|-------------------|
| Antipsychotic dispensing                          | Number of days with antipsychotic prescriptions in the last week (count, range 0 – 7) | RAI               |
| Secondary prescribing outcomes             |                                                                                       |                   |
| Antipsychotic prescribing                         | Any antipsychotic Rx during the past month (dichotomous)                              | ODB               |
| Mean Antipsychotic dose                           | Dose equivalent of antipsychotic dispensed in the past month (continuous)             | ODB               |
| Benzodiazepine (or z-drug) prescribing            | Any Rx during the past month (dichotomous)                                            | ODB               |
| Anti-depressant prescribing                       | Any Rx during the past month (dichotomous)                                            | ODB               |
| Acetaminophen prescribing                         | Any Rx during the past month (dichotomous)                                            | ODB               |
| Secondary clinical outcomes                |                                                                                       |                   |
| Difficulty in performing activities               | ADL long form scale (continuous variable, range 0-28)                                 | RAI (ADL_long_cc) |
| Aggressive behaviour scale                        | Extent of aggressive behaviour (continuous variable, range 0-12)                      | RAI (ABS_cc)      |
| Pain                                              | Pain scale (continuous variable, range 0-3)                                           | RAI (PAIN_cc)     |

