| Depression                                        | Depression rating scale (continuous variable, range 0-14)                             | RAI (DRS_cc)      |
| Falls                                             | Number of falls in the past month (count)                                             | RAI (J4: a)       |
| Secondary health care utilization outcomes |                                                                                       |                   |
| ER visits                                         | Number of ER visits during the previous 6 months (count)                              | CIHI/NACRS        |
| Hospitalizations                                  | Number of hospital visits visit during the previous 6 months (count)                  | CIHI              |

All **primary and secondary prescribing outcomes** will be assessed at baseline (pre-intervention) and at 3 and 6 months post-intervention. Here, "baseline" is defined as the week or month immediately prior to randomization, while post-intervention measurements are defined as the third and sixth months after randomization. These outcomes will be assessed on all residents who are alive at the time of the assessment and who were present in the home for the full duration of the prior week/month.

All **clinical outcomes** (e.g., ADL, behaviour scale, depression, falls) will be assessed at baseline and at 3 and 6 months post-intervention. The most current data collected immediately prior to the implementation of the intervention, and at each post-randomization time point will be used, regardless of mortality status at the subsequent time point.

All **health care utilization outcomes** (number of ER visits and hospitalizations during the previous 6 months) will be assessed at baseline and at 6 months post-intervention. A longer duration is required to allow adequate time for the intervention to have an effect on these outcomes. All residents present in the homes at any time during the study will contribute to the analysis using person-time of follow-up. As the EO intervention may be rolled out over a 2-3 month period due to logistical restraints, homes allocated to the control arm will have their measurement times assigned randomly from the assessment times of the intervention homes in the same stratum.

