Potential effect modification by ownership status of LTC home and staffing ratios, size of the home (<65 beds, 65-129 beds, or >129 beds), location (urban/rural), specialist utilization (proportion of patients with geriatrician or psychiatrist consultation within 6 months), plus primary physician characteristics (sex, years' experience), as well as patient characteristics (age, sex, time at facility, levels of function and aggressive behaviour plus whether a geriatrician or psychiatrist provided a consult) will be explored by including interactions between these variables and: time, treatment, and treatment by time.

Although primary analyses will examine outcomes for all patients excluding those with known to be palliative or with a history of bipolar disorder, schizophrenia or Huntington's disease, planned sub-group analyses will focus on those with dementia. A planned sensitivity analysis will restrict the educational

outreach cohort to physicians who also accessed the audit and feedback to examine for synergy in the full intervention group. We do not anticipate substantial missingness on prescribing or health care utilization outcome; however, exploratory analyses will be carried out to identify the extent of missing data on resident clinical and demographic variables (e.g., levels of function, aggressive behaviour, depression). If more than 5% of residents have missing data at any time, we will create a complete data set for analysis using multiple imputation, where the imputation model will include all covariates of interest in subsequent primary and secondary outcome analyses, as well as those variables identified as associated with missingness.

Since the CCRS data is only released for linkage at ICES annually, a planned interim analysis will compare the primary and secondary prescribing outcomes (which use ODB data). No stopping rules are planned based on this interim analysis; the results will be considered tentative and used only for confidential reporting to the funders.

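### The primary outcome is timed to a single week or month, but its source, the RAI, is completed only about every 3 months, so the stated windows miss most residents

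*Protocol*

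**What the plan says.** The outcomes table (Protocol, Outcomes) defines the primary outcome as "Number of days with antipsychotic prescriptions in the last week", a count from 0 to 7, with RAI as its only source. The other prescribing outcomes in the table come from the drug benefit database (ODB).

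Under Data collection, a full RAI is done within 2 weeks of admission and then "every 12 months from previous full assessment or any other time when the clinical condition of a patient changed considerably". In addition, "each resident also receives a ‘quarterly’ assessment every 3 months".

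The text below the outcomes table sets one timing rule for the primary and secondary prescribing outcomes together: baseline "is defined as the week or month immediately prior to randomization, while post-intervention measurements are defined as the third and sixth months after randomization". The next sentence applies these outcomes to all residents who are alive and were in the home for the whole of the prior week or month.

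The following paragraph has a different rule, stated for clinical outcomes only: "The most current data collected immediately prior to the implementation of the intervention, and at each post-randomization time point will be used".

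Under Analysis the protocol says "We do not anticipate substantial missingness on prescribing or health care utilization outcome". The last paragraph on quantitative analysis plans an interim comparison of the primary and secondary prescribing outcomes and describes them, in parentheses, as using ODB data. The Power section assumes 120 residents per home.

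**The concern.** A week or month window suits dispensing records, which can be read for any date range. It does not suit an item recorded about once a quarter per resident. Taken literally, the protocol admits only residents whose RAI falls inside the window, yet it says all residents are assessed, expects little missing prescribing data and counts 120 residents per home for power. The one rule that would work for RAI items is reserved for the clinical outcomes.

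At stake are the precision of the primary analysis and the freedom left to the analyst. If the rule is not settled in advance, someone must decide which RAI counts for the primary endpoint once the data are in hand.

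**Working it through.** **Inputs from the protocol.** Routine RAI every 3 months; 45 independent clusters (30 intervention, 15 control); 120 residents per home; ICC 0.01; cumulative OR 0.6; 30% of control residents at 7 days; 5% significance level. **Assumptions.** A quarter is 91 days, assessment dates are spread evenly over it, and the test is two-sided.

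**1. The plan's own figures.** An OR of 0.6 applied to 30% gives odds 0.6 × 0.30/0.70 = 0.257, a proportion of 20.5%, which agrees with the stated 20%. The stated 80% power does not reproduce: a 6-month comparison with 120 per home at ICC 0.01 gives 99.9%. That is a separate matter. The comparisons below use the same method with and without the windows.

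**2. Share of residents captured** = window length / assessment interval.
- Baseline, week: 7/91 = 7.7%; 120 × 7/91 = 9.2 residents per home.
- Baseline, if the month is meant: 30/91 = 33%.
- Each follow-up month: 30/91 = 33%; 120 × 30/91 = 39.6, about 40 per home.
- Intervals of 84 to 92 days give 8.3% to 7.6% for the week and 36% to 33% for the month.
- If admission and change-of-condition assessments added 10% to 25% (an assumption), capture would be about 8% to 10% and 37% to 42%.
- A simulation with up to 14 days of jitter in assessment dates gave the same 7.6% to 7.7% and 33%. A look-back of one full cycle captured every resident on a quarterly schedule.

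**3. Power, difference in change from baseline.** Design effect DE = 1 + (m − 1) × 0.01; effective sizes n_C = 15m/DE and n_I = 30m/DE.
- Baseline variance of the log OR: 1/(n_C × 0.30 × 0.70) + 1/(n_I × 0.30 × 0.70).
- Follow-up variance: 1/(n_C × 0.30 × 0.70) + 1/(n_I × 0.205 × 0.795).
- Power = Φ(0.511/SE − 1.96), where 0.511 = |ln 0.6|. No correlation between periods is assumed.

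| Residents per home, baseline / follow-up | Variance | SE | Power |
|---|---|---|---|
| 120 / 120 | 0.0087 + 0.0095 | 0.135 | 97% |
| 9.2 / 40 (week, then month) | 0.0560 + 0.0182 | 0.272 | 47% |
| 40 / 40 (month throughout) | 0.0165 + 0.0182 | 0.186 | 78% |

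At the other extreme, if the home effect cancelled completely between periods (no design effect), the SE would rise from 0.091 to 0.255 and power would fall from about 100% to 52%; month windows throughout would give about 90%. At ICC 0.05 the fall from full data to 9.2 / 40 is from 57% to 33%.

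**4. Power, 6-month contrast alone.** With 40 per home, DE = 1.39, the follow-up variance is 0.0182 and the SE is 0.135. Power is about 96%, against 99.9% with 120.

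**The case against.** **The week or month may be a look-back period, not an admissible RAI date.** The phrase covers both last-week and past-month outcomes, and the next sentence ties the prior week or month to the assessment. A quarterly RAI also fits the 3-month spacing. This may well be what was intended. But the text equates baseline with the period just before randomization and follow-up with named months, and the rule that would pick the nearest RAI is confined to clinical outcomes. The intention has to be written down.

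**The primary outcome may come from ODB after all.** The parenthesis on the interim analysis can be read that way, and it would make the windows workable. It can equally refer only to the secondary prescribing outcomes. The outcomes table gives RAI alone, so the two places must be reconciled.

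**The power loss depends on the model.** This stands. The primary effect is expressed as an OR at 6 months, and change from baseline is described in the Power section only for the dichotomous outcome. A reader might infer that the trial loses half its power; that holds only for a difference in change with the one-week baseline.

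**Imputation.** A reader might infer that nearly all baseline outcome values would have to be imputed. The documents do not establish this. Imputation is tied mainly to covariates and to resident clinical and demographic variables, and the default design is cross-sectional, where a resident not assessed in the window is not necessarily a missing outcome.

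**Selection.** Residents assessed in a narrow window may over-represent changes in condition. The protocol gives nothing to size this, and the requirement of presence for the full prior week or month limits the share of new admissions. No bias between arms is shown.

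**Clinical outcomes.** The most-recent rule has no maximum age, so a 3-month value falls on average about 45 days after randomization and a late assessment could bring in a pre-randomization value. This is minor and mainly affects month 3; by month 6 the latest RAI would typically fall in days 92–183.

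**Windows belong in the statistical analysis plan.** Detail does. Here, though, the protocol itself fixes a rule that its named source cannot meet.

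**Conclusion.** The contradiction holds. The timing rule for the primary outcome cannot deliver all residents from an assessment done about once every 91 days. With evenly spread assessments it yields about 7.7% of residents at baseline, or a third if the month applies, and about a third at each follow-up; the modest range from other intervals or extra assessments does not change this. The effect on power ranges from slight (about 96% for a 6-month contrast) to severe (47% for a difference in change with a one-week baseline), both for OR 0.6 at ICC 0.01. The point is therefore an unworkable definition of the primary endpoint with a possible large loss of precision. It is not a demonstrated loss of the trial's power or a demonstrated bias.

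**What to change.** For the primary outcome, replace the week/month timing with one RAI per resident per window of about one assessment cycle:
- **Baseline:** the last RAI in roughly the 92 days before time zero.
- **3 and 6 months:** the RAI in non-overlapping post-randomization windows of about one cycle each, with no pre-randomization RAI counted as follow-up.
- **Time zero:** define it for both arms under the staggered rollout, including control homes, whose measurement times are drawn from intervention homes in the same stratum.
- **End of the 6-month window:** before the falls topic starts in that home, for example days 92–183 where timing allows. Day 183 after a 31 October 2015 randomization is 1 May 2016, at the edge of the May–June start shown in the Implementation chart; a window running to day 228 would reach 15 June. For Phase 2 homes, allocated in March–April 2016, the chart puts the falls topic well before month 6, so no choice of window removes that overlap and the plan should say so.

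Apply the same windows to the RAI clinical outcomes, keep the past-month rule for ODB outcomes, and reconcile the interim-analysis remark about ODB data with the RAI source in the outcomes table.

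The cost is wording only, with no new data. The downside is that each measurement refers to a window rather than a fixed date, and values early in the first follow-up window reflect little exposure.

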### **Prescriber Survey:**

The survey will be administered by the evaluation team to the LTC home leadership. At the time of study launch and after 6 months, the evaluation team will distribute the survey, asking home leadership to complete it themselves in addition to forwarding the survey to the prescribers and pharmacists. The evaluation team will also send a series of weekly reminders to home leadership, for a total of three weeks, to encourage completion.

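### The Outcomes section mixes time origins: clinical baselines run from outreach implementation but follow-up runs from randomisation, so one RAI record can serve as both baseline and 3-month value

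*Protocol*

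**What the plan says.** Timing is set in the paragraphs after the outcomes table in the protocol's Outcomes section.

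- **Primary and prescribing outcomes.** These "will be assessed at baseline (pre-intervention) and at 3 and 6 months post-intervention". The terms are then defined: baseline "is defined as the week or month immediately prior to randomization", and "post-intervention measurements are defined as the third and sixth months after randomization".
- **Clinical outcomes** (function, aggressive behaviour, pain, depression, falls). "The most current data collected immediately prior to the implementation of the intervention, and at each post-randomization time point will be used".
- **Utilisation outcomes.** Assessed at baseline and 6 months. The paragraph closes with a rollout rule: "As the EO intervention may be rolled out over a 2-3 month period due to logistical restraints", control homes have their "measurement times assigned randomly from the assessment times of the intervention homes in the same stratum".

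Elsewhere, Data collection says that "each resident also receives a ‘quarterly’ assessment every 3 months", on top of full assessments at admission, yearly and after a marked change in condition. The Analysis section reads the primary effect at 6 months and handles the stagger with a fixed effect for phase. The Implementation timetable shows Phase 1 allocated in September-October with 6-month follow-up complete in March-April, and Phase 2 allocated in March-April with follow-up complete in September-October.

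**The concern.** Time zero decides which record enters each baseline and follow-up cell, in both arms. The section gives more than one.

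Two things follow if outreach in a home starts some time after randomisation. First, on the randomisation clock, the nominal 3 and 6 months are not 3 and 6 months of outreach. Second, the clinical rule measures from a later baseline to an unmoved follow-up point. The gap is then shorter than one quarterly RAI cycle, and for some residents the latest record before implementation is still the latest record at 3 months. Their change is zero by construction.

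The clinical rule also permits a baseline recorded after randomisation. Control homes have no implementation date of their own, so the rule gives them no baseline unless the drawn times are meant to supply it. The text does not say so.

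**Working it through.** **1. The anchors side by side**

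| Outcomes | Baseline tied to | Follow-up tied to |
|---|---|---|
| Primary, prescribing | randomisation | randomisation, though labelled post-intervention |
| Clinical | implementation of outreach | post-randomisation time points |
| Utilisation | the intervention (Analysis section) | the intervention; randomisation not mentioned |
| Control homes | not stated separately | times drawn from intervention homes |

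All of these coincide if outreach starts on the day of randomisation. They separate once it starts later.

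**2. Exposure on the randomisation clock**

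Inputs: follow-up at T = 3 and 6 months and a rollout of 2-3 months (both from Outcomes). Assumption: the rollout window opens at randomisation, so a home starts s months later, with s between 0 and 3. Exposure = T - s. For starts uniform over 0 to W months, mean exposure = T - W/2.

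| Start | Exposure at 3 months | Exposure at 6 months |
|---|---|---|
| s = 0 | 3 | 6 |
| s = 1 | 2 | 5 |
| s = 2 | 1 | 4 |
| s = 3 | 0 | 3 |
| uniform 0-2, mean | 3 - 1 = 2.0 | 6 - 1 = 5.0 |
| uniform 0-3, mean | 3 - 1.5 = 1.5 | 6 - 1.5 = 4.5 |

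The protocol's nominal 3 and 6 months are reproduced only at s = 0, or if follow-up runs from outreach start.

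**3. Reuse of one RAI record for clinical outcomes**

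Assume one RAI every 3 months, dates spread evenly over the cycle, and no extra assessments. The chance of a new record between s and month 3 is (3 - s)/3, so the chance of reuse is s/3.

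- s = 0: 0%; s = 1: 33%; s = 2: 67%; s = 3: 100%.
- Mean for uniform starts is (W/2)/3 = W/6: 2/6 = 33% for 0-2 months and 3/6 = 50% for 0-3 months.

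Admission and change-of-condition assessments lower these figures.

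**4. The primary outcome**

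Its baseline precedes randomisation, so baseline to the 3-month point is a full 3-month cycle. With on-schedule RAIs, reuse is about 0%.

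**5. Direction of any bias at 3 months**

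Let c be the control change, c + d the outreach change, and r the reuse share, treating residents with and without reuse as alike.

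- Reuse in outreach homes only: (1 - r)(c + d) - c = d - r(c + d). The shift, -r(c + d), depends on the control trend and can go either way.
- Controls on matched times, with the same r: (1 - r)(c + d) - (1 - r)c = (1 - r)d, which is attenuation.

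The sign therefore depends on the control trend and on how control times are applied, and the protocol settles neither.

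**The case against.** The strongest reply is that timing from randomisation is a legitimate intention-to-treat choice. The trial is pragmatic, the number and length of visits are deliberately left open, and delay in delivery is part of the policy being tested. That stands. Shorter exposure is then not a defect in itself; the defects are the post-intervention label and the clinical baseline that leaves the randomisation clock.

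The documents do not support four stronger readings.

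- **A reader might infer that the nominal exposure is not delivered.** The delay from randomisation to outreach is not stated, the rollout is put permissively, and if a rollout clock was intended, both the shortfall and the reuse largely vanish. The control-time draw does not settle which clock governs. The Implementation timetable shows two allocation periods, with the audit-and-feedback-only row in Phase 1, so intervention homes can have different calendar times even on a randomisation clock. The reason given for the draw is, however, the 2-3 month rollout, and the phases are about six months apart.
- **A reader might infer that all results are pulled toward no effect.** The expressions in the working show that this does not follow.
- **A reader might infer that the 6-month utilisation window includes months before outreach.** Neither Outcomes nor Analysis ties that window to randomisation.
- **A reader might see a third clock in the prescriber survey**, where "At the time of study launch and after 6 months, the evaluation team will distribute the survey". This is a process measure, and Data collection places its first round before intervention delivery. It is minor.

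Reuse is also confined to secondary clinical outcomes at the intermediate time point. That group does include falls, which the Objectives name in the primary question although the outcomes table lists them as secondary.

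**Conclusion.** The point holds as an internal contradiction of moderate severity. Outcomes ties the clinical baseline to implementation and clinical follow-up to randomisation, and it labels randomisation-based time points as post-intervention. That much needs no assumption.

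The size is conditional on the randomisation clock governing, on a start delay of 0-3 months that the documents do not give, and on quarterly RAIs kept to schedule. Mean exposure would then be 1.5-2.0 months at the 3-month point and 4.5-5.0 months at the 6-month point. On average 33-50% of residents in outreach homes would have one RAI in both clinical cells at 3 months. The phase term in the model cannot absorb a delay that varies between homes within a phase. The primary outcome is not exposed to reuse, and no sample-size figure changes.

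**What to change.** Amend Outcomes to state one time origin per allocation unit (homes sharing prescribers counted together), used for baseline and follow-up in both arms. Take the clinical baseline, like the prescribing baseline, as the last RAI before randomisation. Require each follow-up RAI to be dated after the origin and to be a different record from the baseline. Then choose one option.

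- **(a) Randomisation clock.** Relabel the time points as post-randomisation, and drop or justify the control-time draw. The cost is wording only.
- **(b) Scheduled outreach date.** Use the date fixed at allocation, not the actual start, with control dates drawn within stratum, and correct the definition that runs from randomisation. This needs one date variable per unit and later data extraction for late-start homes. It is open only if scheduled dates were recorded at allocation; this protocol version, dated 30 May 2016, follows both allocation periods in the timetable.

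Option (b) has two downsides to state. Baseline-to-follow-up intervals would vary by home. Late Phase 1 follow-up could also run into the falls topic: allocation in September-October plus 2-3 months plus 6 months gives May to July, and the timetable introduces Topic 2 in May-June. As the timetable reads, Phase 2 follow-up overlaps Topic 2 on either clock.

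The choice should be recorded before outcome data are compared by arm, including the planned interim look at prescribing outcomes.
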